#### Objectives

This study aims to:determine the implementation fidelity of each intervention component,assess the effect of each component on corresponding proximal outcomes,examine the effect of each component on primary outcomes (e.g. depression, burden),determine if the proximal outcomes of each component mediate the components’ effects on primary outcomes,determine the interaction effect between components on their proximal and primary outcomes anddetermine the moderating effect of the baseline scores of primary outcomes in the relationship between each intervention component and the corresponding outcome.

The hypotheses to be tested are as follows:The implementation fidelity of all six components is equally high.Components 2 (self-care skills), 3 (behavioural symptom management), 4 (behavioural activation), 5 (modified mindfulness-based cognitive therapy) and 6 (support group) will have significant effects on proximal outcomes, namely, self-care, dementia caregiving strategy, engagement in pleasurable activity, mindfulness and satisfaction with support group, respectively.Components 2–6 will have a stronger effect on their corresponding primary outcomes, namely, physical health status, stress/burden, psychological well-being, anxiety/depressive symptoms and social support, respectively, than the other components.Self-care, dementia caregiving strategy, engagement in pleasurable activity, mindfulness and satisfaction with support group mediate the relationship between component 2 and physical health status, between component 3 and stress/caregiving burden, between component 4 and psychological well-being, between component 5 and anxiety/depressive symptoms and between component 6 and social support, respectively.Component 3 moderates the relationship between component 6 and social support.The baseline scores of physical health status, stress/burden, psychological well-being, anxiety/depressive symptoms and social support moderate the effects of components 2–6 on changes in scores between the baseline and follow-up assessments of the corresponding outcomes.

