#### Allocation concealment, assignment of interventions and blinding

After baseline assessment, all participants will receive component 1 (dementia and caregiver education) as the core intervention. Participants will be randomly assigned to one of the 16 ECs (Table 1) by using the fractional factorial MOST design. Computer-generated random numbers will be used for allocation. Participants will be informed of their assigned group by an independent person not involved in the assessment. The allocation list will be computer-generated by an independent researcher and concealed from other researchers and participants until the time of assignment. Outcome assessors will be blinded to participant group allocation. Unblinding should only occur for participant safety concern when a series adverse event transpires and knowledge of the assignment of intervention could mitigate the health risk (Fig. 1) [24].

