#### Data analysis

This study will adopt the principle of intention-to-treat for data analysis of the individual intervention components (components 2–6). The main objective is to examine the level of significance of each factor on proximal and primary outcomes by using linear mixed models at three time points (T0, T1 and T2). Linear mixed regression models account for repeated measures within participants and handle missing data using maximum likelihood estimation in a longitudinal dataset without needing multiple imputations [51]. The pre − post within group difference will also be investigated (i.e. T1 vs. T0 and T2 vs. T0). On the one hand, the across time difference of each component can be viewed as the main effect. On the other hand, such effect will be modelled as components by time interactions, with T2 outcome as the primary endpoint. The study will also include the analysis for two-way interactions between components (i.e. factor 3 by factor 6 by time interaction).

The examination of moderation and mediation effects of significance will follow the guidelines established by MacKinnon and Luecken [52]. To detect the underlying mechanism of components, the study will test for fit of the mediation model. The relationship path between each component and their respective primary outcomes will be established. The pathway between the components and proximal outcomes and between the proximal and primary outcomes will be investigated. The relationship between the components and primary outcomes mediated by the proximal outcomes will be investigated. When testing the fit of the moderation model, the relationship between each component and the change of primary outcome will be examined. Afterwards, the strength and direction of the relationship will be tested again accounting for the effects of the baseline primary outcomes. The moderation models will be used to identify the interaction effects of the matching risk profiles of caregivers with specific components. The moderating effects of the matching profiles with components have never been explored in previous studies.

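### The moderation steps as written adjust for baseline instead of testing a component-by-baseline interaction, so they do not deliver the stated moderation aim

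*Protocol article*

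**What the plan says.** The sixth aim and the last hypothesis (Objectives) state effect modification: baseline scores on the primary outcomes are expected to "moderate the effects of components 2–6 on changes in scores between the baseline and follow-up assessments of the corresponding outcomes".

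The Data analysis section gives the procedure. In the first step, "the relationship between each component and the change of primary outcome will be examined". In the second step, "the strength and direction of the relationship will be tested again accounting for the effects of the baseline primary outcomes". The next sentence gives the purpose: "The moderation models will be used to identify the interaction effects of the matching risk profiles of caregivers with specific components". The paragraph opens with a general reference to a published source: "The examination of moderation and mediation effects of significance will follow the guidelines established by" the authors of a cited methods paper.

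On allocation, the protocol says: "Participants will be randomly assigned to one of the 16 ECs (Table 1) by using the fractional factorial MOST design". This happens after the baseline assessment.

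**The concern.** Testing a relationship, and then testing it again with a third variable accounted for, answers whether that variable explains or confounds the relationship. Moderation is a different question: does the size of the component's effect depend on the baseline score? Only a term that lets the effect vary with baseline can answer it, and neither written step contains one. Elsewhere in the same section, for components 3 and 6, the authors do name an interaction with time when they mean one.

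At stake are the sixth aim, the last hypothesis, and the plan to match components to caregivers' risk profiles, which the Introduction and the Conclusion both present as a route to personalised support. An analyst who followed the two steps literally would finish them without an answer to the moderation question.

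**Working it through.** **The plan's own figure.** The Sample size estimation section gives 200 analysed for an effect of 0.40 with 80% power, two-tailed. Per component level, n = 2(1.96 + 0.84)²/0.40² ≈ 98.1, rounded up to 99, so 198 in total against 200 stated. Adding 20% attrition, 200/0.8 = 250, as stated. This uses alpha 0.05; the printed alpha of 0.5 would give 58 in total. The 0.40 is quoted for a main or interaction effect and is not tied to baseline moderation, so the article gives no figure for this test.

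**Model for the check.** Let B be the standardised baseline score, A = ±1 the randomised component, m the average effect and g the shift in effect per SD of baseline:

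- Y = ρB + (m/2)A + (g/2)AB + e, with change C = Y − B.
- Inputs: N = 200 (document), m = 0 or 0.40 (0.40 from the document), ρ = 0.5 and g = 0, 0.2 or 0.4 (assumptions).

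**Expected values.** The mean difference in C between the two component levels is m + g·E(B). With B centred, E(B) = 0 and the difference is m. Because A is independent of B, adding B to the model leaves that expectation at m. So steps 1 and 2 both estimate m, and g appears in neither. It appears only as the coefficient of the product AB. Since B is in the model, that coefficient is the same for C as for Y.

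**Simulation.** 5,000 trials per row, showing the percentage with p < 0.05:

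| Average effect m | Shift g | Step 1: component only | Step 2: component + baseline | Product term |
|---|---|---|---|---|
| 0 | 0 | 4.8 | 5.1 | 5.4 |
| 0 | 0.2 | 4.9 | 4.9 | 36.7 |
| 0 | 0.4 | 5.2 | 4.9 | 89.3 |
| 0.4 | 0 | 79.6 | 89.3 | 5.1 |
| 0.4 | 0.4 | 77.9 | 88.4 | 88.6 |

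- Step 2 follows m and ignores g: with m = 0.4 it rejects in 89.3% without moderation and 88.4% with it.
- The mean estimated effect before and after adjustment is 0.400 and 0.398 (g = 0), and 0.399 and 0.401 (g = 0.4).

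**Hand check of the product term.** Residual variance is 1 − 0.5² = 0.75, so the standard error is √(4 × 0.75/200) = 0.122. For g = 0.4, 0.4/0.122 = 3.27 and power ≈ Φ(3.27 − 1.96) = Φ(1.31) ≈ 0.90. For g = 0.2, power ≈ Φ(1.63 − 1.96) = Φ(−0.33) ≈ 0.37. Both agree with the table.

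**Differences within one trial.** Step 1 and step 2 estimates differ only through chance imbalance in B. The SD of the difference is |ρ − 1| × √(4/200) = 0.5 × 0.141 = 0.071; the simulation gives 0.07. A visible change in the estimate after adjustment is therefore noise and carries no information on g.

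**Sensitivity.** A separate simulation with ρ = 0.6, m = 0.40 and 4,000 trials per scenario gives the same picture. The component effect is about 0.40 before and after adjustment throughout, while the product term rejects in 4.9%, 40.7%, 73.5% and 92.4% of trials for g = 0, 0.2, 0.3 and 0.4.

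**The case against.** The best defence is that the aim is clear. The sentence after the two steps names interaction effects, the hypothesis is worded as effect modification, and a moderation guideline is cited. A condensed article may leave the exact model term to the analysis plan, and the phrase about strength and direction can be read as a loose description of a moderator.

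Part of this stands. A reader might infer that the plan as a whole has settled on a test that cannot detect moderation. The documents do not support that, because the stated aim is an interaction and the cited guideline is not at hand. What remains is a mismatch: the article writes out a procedure, and that procedure does not produce what the next sentence promises. A general citation does not correct explicit steps.

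Two further readings are tempting and also unsupported.

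- A reader might infer that working with change loses everyone without follow-up, up to 50 of 250, against the intention-to-treat principle. No complete-case rule is stated. The section says that its mixed models "handle missing data using maximum likelihood estimation in a longitudinal dataset", without saying whether this covers the moderation models. The 20% attrition is already in the sample size. Participants with baseline only would add little in any case: under assumed variances, the standard error was 0.0676 with 50 such participants and 0.0693 without them, a ratio of 1.025. A model of follow-up scores with baseline as covariate would not use them either.
- A reader might infer that a p-value which turns significant after adjustment will be taken as moderation. Rejection does rise without any moderation, from 79.6% to 89.3% above, because residual variance falls. But nothing in the article says that such a change will be interpreted in that way.

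It is also fair that the aim is not primary: the Discussion lists the matching of treatments to individual characteristics among the secondary objectives.

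**Conclusion.** The concern holds as a mismatch between procedure and aim. The two written steps are covariate adjustment and, with randomised components, carry no information on whether baseline modifies a component's effect. That conclusion follows from randomisation and does not depend on the assumed correlation or effect sizes. The size of the gap does depend on them: with 200 analysed, correlation 0.5 and no average effect, the adjusted re-test stays at 4.9% for a shift of 0.2 or 0.4 SD per SD of baseline, while the product term reaches 36.7% and 89.3%. The article gives no baseline-to-outcome correlation or expected moderation size, so these figures illustrate the gap and do not correct any stated number.

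The main component effects, the sample size and the missing-data plan are not affected. The correction is worth making because a secondary aim and its hypothesis have no valid test in the steps as worded.

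**What to change.** Replace the second step with a named interaction test. For each component's matched primary outcome, fit a model with the baseline score, the component main effects and the component-by-baseline-score product, inside the mixed-model framework already planned (component × baseline × time). Read the term at T2, which the Data analysis section names as the primary endpoint. State that any moderation claim rests on this term alone, and not on comparing a component's effect before and after adjustment.

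One detail for the analysis plan: a score that acts as moderator reproduces its own T0 row exactly, so the plan should say how T0 enters these particular models.

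The cost is the wording of one paragraph and slightly more model code. No new data, visits or participants are needed. The power of the product term is not covered by the stated sample size calculation, so results should be reported with confidence intervals and described as secondary.

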#### Ethical considerations and dissemination

The research has been approved by the Institutional Review Board of the Education University of Hong Kong, Human Research Ethics Committee (IRB number: A2020-2021–0045). This study is registered retrospectively in the WHO Primary Registry – Chinese Clinical Trials Registry (ChiCTR2300071235). Protocol amendments, if any, will be submitted to the ethics committee for review. Protocol amendments will only be applied after obtaining ethics approval. This trial does not involve collecting biological specimens for storage. The study aims, intervention content, voluntary participation and right to withdraw at any time will be explained verbally and outlined in detail on the information sheet. The researcher will emphasise that their decision to join/refuse/withdraw from the study will not affect the routine care and services provided by the community centres/outpatient clinics. Each participant will be given a subject code, and no identifiable information will be presented in the data file to protect participants’ confidentiality. All the data collected will be stored in a secure place and can only be accessed by the research team members. There is no anticipated harm and compensation for trial participation. The trial will be conducted in accordance with the Declaration of Helsinki and reported in accordance with the CONSORT guideline and its extension to non-pharmacological interventions [53].

Results will be disseminated via presentations at scientific conferences, peer-reviewed publications, public engagement events, stakeholder organisations, patient support groups and other forms of media where appropriate. The investigators will be involved in reviewing drafts of the manuscripts, abstracts, press releases and any other publications arising from the study. The study protocol will be published in an open access journal so that the public can access to the full protocol. All authors read and approved the final manuscript.

### Discussion

As the dementia tsunami approaches, effective family caregiver interventions are essential to improve the health outcomes of the caregiver–care recipient dyads and delay nursing home placement. Multicomponent interventions are promising strategies to support dementia caregiving but will provide a bundled treatment package, which may be associated with increased cost if inactive components are provided or if more than what is necessary is delivered. By using the MOST framework, we can identify the individually effective components of multicomponent interventions for dementia caregiving. This proposed study extends and clarifies our prior work [8–10, 13, 15, 54], indicating the efficacy of a multicomponent package of interventions to support the physical and psychosocial well-being of dementia caregivers.

We have described the protocol for a MOST fractional factorial trial aimed to optimise the multicomponent interventions for dementia caregivers. The primary objective of this study is to estimate the specific effect of each of the five components on its corresponding primary outcomes within 6 months and propose the most effective and efficient combination of components for dementia caregivers. The study has several secondary objectives, including the exploration of implementation fidelity, the main effects and the interactions of each component and the matching between treatments and individual characteristics to support dementia caregivers over the course of 12 months. The proposed trial is significant in representing the first principled and systematic effort to design an effective, efficient and potentially personalised intervention to meet the modest demands of dementia caregivers, such that all of its components (education, training on self-care skills, behavioural symptom management, behavioural activation, mindfulness and support group) are active and feasible for real-world implementation.

#### Limitations

The two main challenges we anticipate are related to the complexity of subject allocation and the pragmatic nature of the study. Following the MOST framework with a fractional factorial design, we are randomising participants to one of 16 conditions. Therefore, preventing contamination across conditions and monitoring the implementation fidelity of each condition are challenging.

Contamination may arise if a participant learns what other components a fellow participant is receiving, which might be most likely to occur in the study waiting areas and in the support group component when participants from different ECs come together for sharing [55]. Participants may feel disappointed or disgruntled by their treatment in the study relative to other participants, which may lead to ‘resentful demoralisation’ and potentially reduced motivation to engage in the study. In addition, participants may be triggered to pursue similar types of activities or seek additional information outside of the study to compensate for what is not being received. Although eliminating contamination fully is infeasible, we will adopt several strategies to minimise it. Firstly, participants will be informed at enrolment that the treatment conditions will be varied among participants to manage expectations. The information provided in the informed consent form will follow the principle of equipoise by declaring uncertainty about the superiority of the treatment effect of all experimental conditions [56]. We will also ask all the participants not to disclose their group status nor discuss any specifics of study components with other participants at any time point. For the support group session, the facilitator will attend to and encourage discussion among the four proposed themes; any discussion of other components by participants in the groups will be discouraged [57].

The second challenge relates to the fact that this study is a pragmatic trial embedded within usual care from multiple sources of recruitment, and we may lose the ability to tightly control the use of each condition. For example, if a participant chooses not to follow the use of behavioural activation strategies, we will not be able to enforce their usage. Although this may make assessment of outcome data difficult (i.e. effectiveness of a condition that is insufficiently used), this situation reflects how the conditions may be used in the ‘real world’. To address this concern, we will monitor the implementation fidelity of each component. Interventionists will rate caregivers’ enactment in four aspects: data collection, home assignments, use of notebooks and use of written prescriptions [58]. In addition, a satisfaction questionnaire will be conducted postintervention to collect information about participants’ satisfaction with specific components and with the quality of services [56].

### Conclusion

This study uses the MOST framework to optimise the provision and delivery of a multicomponent intervention to support family dementia caregivers. The examination of the implementation fidelity, the main effects and interactions of individual components and the underlying moderating mechanism of multicomponent interventions will be useful for future investigations to optimise family caregiver interventions for implementation and dissemination. The study findings will help develop cost-effective, personalised prescription of caregiving support programmes, which in turn, will enhance caregivers’ physical health and psychological well-being, improve the provision of social support, help them to tackle issues of stress, anxiety and depressive symptoms and ease their burdens in caring for people with dementia, thereby reducing the costs of health care and long-term care.

### Trial status

This study was retrospectively registered in the WHO Primary Registry – Chinese Clinical Trials Registry (ChiCTR2300071235). (Protocol date 30/10/2020; version identifier 2020–2021-0045). Registered 9 May, 2023. https://www.chictr.org.cn/showprojEN.html?proj=194600 This is an on-going trial (as date of protocol manuscript submission). Participants were recruited from Jun 1, 2021, to Dec 31, 2022; and the last participant follow-up visit would be on Nov 30, 2023.

## Data Availability

The data that support the findings of this study are available from [name] upon reasonable request.
